### Participants

Setting: Primary Health Care. Valencian Community (Spain).

15 Health centers: Alicante-Cabo-Huertas, Alicante-Campello, Alicante-Plà Hospital, Castellón-Dolores-Cano-Royo-Villareal, Castellón-La-Bobila-Villareal, Castellón-Cariñena-Villareal, Castellón-Nules, Castellón-Vall d’Uxo I and II; Valencia-S Pau, Valencia-R-Argentina, Valencia-Benimaclet and Valencia-Serreria-II.

Inclusion criteria: patients with a diagnosis of IHD of any site (ICD-10 codes from 410 to 414 inclusive); age from 30 to 80 years; signed written informed consent. Exclusion criteria: lack of consent; immobilized patients; patients with serious health problems or with a low life expectancy.

Data are collected from electronic health record system.

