### Randomization, allocation and implementation

Valencia is a Mediterranean Spanish Region with 5 million inhabitants. In 2007, 800 primary care physicians and nurses started the ESCARVAL primary prevention cohort study [20]. 72 Health centers (HC) participated including 50000 patients.

For the intervention group in the PROPRESE study 15 HC are selected from those participating in ESCARVAL. Once the center agreed to participate patients are randomly selected from the total amount of patients with IHD registered in the electronic health records.

For the control group a random sample of patients with IHD is selected from all 72 HC electronic records.

Patients are enrolled by their primary care physicians who will offer to participate to the randomly selected patient.

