### Blinding

Blinding is not possible as the intervention is a multifactorial approach. That’s why the control group is selected after the intervention is made but for the same period of time.

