### Follow-up

Table 4 shows the follow-up plan and patient data collection. Functions of the professionals participating in the study are described in Table 5.

**Table 4 T4:** Follow-up plan and collection of patient data

			
**Enrolment allocation**	**Intervention group:**		
	15 HC selected from those participating in ESCARVAL-risk study.		
	350 patients randomly selected from the total amount of patients with IHD registered in the electronic health records.		
	Patients are enrolled by their primary care physicians. (Inclusion and exclusion criteria).		

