	**Control group:**		
	A random sample of patients (350) with IHD selected from 72 HC electronic records (from ESCARVAL-risk study)		
**Intervention follow-up: 1 year**	Baseline data		
	Personalized follow-up record		
	Starting formative intervention strategy for professionals and patients:		
	**Intervention**	**Patients**	**Professionals**
	**First visit**	Evaluate monitoring of CVRF	Advice online by cardiologist
		Accord control objectives	Monthly updates
		Adherence control	Protocols, guides and bibliography reviews
		Therapeutic education	In-class training course
	**Second visit**	Evaluate monitoring of CVRF	Advice online by cardiologist
		Accord control objectives	Monthly updates
		Adherence control	Protocols, guides and bibliography reviews
		Therapeutic education	In-class training course
	**Third visit**	Evaluate monitoring of CVRF	Advice online by cardiologist
		Accord control objectives	Monthly updates
		Adherence control	Protocols, guides and bibliography reviews
		Therapeutic education	In-class training course
		Number of hospital admissions	
**Outcomes**	Statistical analysis. Loses to follow-up.		
	Presentation of results at participating HC.		
	Final report		

*HC*, Health Center.

**Table 5 T5:** Functions of the professionals participating in the study

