** *Functions of each professional in the study* **	
** *Primary care physicians/nurses:* **	- Identification of patients to include.
	- Inclusion and contact with patients.
	- Adaptation of therapeutic interventions.
	- Therapeutic compliance.
** *Reference cardiologists and group of experts* **	- Workshop teaching.
	- Online tutorials.
	- Selection of documents, guidelines and protocols.
** *San Juan Alicante Department Research Unit* **	- Analysis of the data and interpretation of the results
** *Abucasis responsible* **	- Facilitate the use of the electronic medical history through response to doubts or information about not very used resources.

Figure 2 provides a flow diagram of the study.

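### The protocol does not make clear that its undefined health exclusions are applied to controls by the same rule and at the same time as to intervention patients, and Table 4 suggests they are not

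*Protocol article*

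**What the plan says.** Some parts of the protocol article read as covering everyone:

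- **Participants** gives a single list that names no arm: "Exclusion criteria: lack of consent; immobilized patients; patients with serious health problems or with a low life expectancy". Serious ill health and short life expectancy are not defined there or elsewhere in the article.
- **Informed consent** requires a signed form from all patients.
- **Randomization, allocation and implementation** states: "Patients are enrolled by their primary care physicians who will offer to participate to the randomly selected patient". The sentence follows the paragraph on controls and is not limited to one arm.

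Other parts treat the two groups differently:

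- **Table 4, intervention group**: "Patients are enrolled by their primary care physicians. (Inclusion and exclusion criteria" (in brackets in the table).
- **Table 4, control group**: "A random sample of patients (350) with IHD selected from 72 HC electronic records (from ESCARVAL-risk study". No enrolment step and no criteria are shown.
- **Randomization, allocation and implementation**: "For the control group a random sample of patients with IHD is selected from all 72 HC electronic records". Again no criteria are named.
- **Blinding**: "the control group is selected after the intervention is made but for the same period of time".

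Table 5 gives primary care physicians and nurses the task described as "Identification of patients to include", without naming an arm. The study is open, and Outcome measures makes hospitalizations the primary outcome.

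**The concern.** Whether a patient is too ill to take part is a judgement when the term has no definition. In the intervention arm, Table 4 has that judgement made after sampling, at entry, by physicians in the participating centers, in an open study. In the control arm it is either absent or has to be made later, when the year is already over.

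Immobilized, seriously ill or short-lived patients are plausibly admitted more often than the rest. If they are filtered out of one arm and not the other, the hospitalization rates differ with no treatment effect. Randomization does not protect against this, because the article describes random sampling from two different frames (15 centers and 72 centers), not random allocation of one eligible pool. The point is separate from the timing of control selection alone: a common date would not help if different rules were applied on that date.

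**Working it through.** **Step 1: the possible readings.** The article gives no figure on this point to reproduce.

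- *Reading A (Table 4 taken literally):* the health exclusions apply to intervention patients only.
- *Reading B (Participants, Informed consent and the general enrolment sentence taken as governing):* they apply to both arms. Under the Blinding section, however, controls are chosen after the intervention, so the exclusions are applied retrospectively, with undefined terms. Intervention patients are judged prospectively.

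Under neither reading does the article show one rule applied at one time.

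**Step 2: size under reading A.** Let f be the share of controls who would have been excluded had they been screened like intervention patients, and k their admission rate relative to the rest. With no true effect:

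spurious rate ratio (intervention/control) = 1 / (1 − f + f·k)

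Both f and k are assumptions, because the article gives neither. The chance of a significant result favouring the intervention uses a two-sided 5% comparison of the proportion admitted. There are 301 per group (Sample size section), and the risk p in eligible patients is assumed to be 10% or 20%. Control risk is p_c = p(1 − f + f·k), and

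chance = Φ[(p_c − p − 1.96·SE0) / SE1]

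where SE0 uses the pooled proportion and SE1 the separate ones. The nominal value is 2.5%. Treating the outcome as admitted or not is a simplification.

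| f | k | 1 − f + f·k | Rate ratio | Chance, p = 10% | Chance, p = 20% |
|---|---|---|---|---|---|
| 5% | 1.5 | 1.025 | 0.98 | 3.2% | 3.5% |
| 5% | 2 | 1.05 | 0.95 | 3.9% | 4.9% |
| 10% | 2 | 1.10 | 0.91 | 5.9% | 8.7% |
| 10% | 3 | 1.20 | 0.83 | 12.0% | 21.9% |
| 20% | 3 | 1.40 | 0.71 | 32.6% | 63.3% |

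Worked row (f = 10%, k = 2, p = 20%): p_c = 0.20 × 1.10 = 0.22. SE0 = √(2 × 0.21 × 0.79 / 301) = 0.0332. SE1 = √((0.20 × 0.80 + 0.22 × 0.78) / 301) = 0.0332. Then (0.02 − 1.96 × 0.0332) / 0.0332 = −1.36, and Φ(−1.36) ≈ 0.087.

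If some controls are screened, f is only the remaining unscreened share. With the same rule in both arms f = 0 and the ratio is 1.00.

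**Step 3: the opposite direction under reading B.** Suppose late selection with consent removes a share g of controls who died or became too ill during the year, while similar intervention patients, enrolled at the start, stay in. With no true effect:

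spurious rate ratio = (1 − g) + g·k

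For g = 5% and k = 2 this is 0.95 + 0.10 = 1.05, against the intervention. For g from 2% to 10% and k from 1.5 to 3 it runs from 1.01 to 1.20. These inputs are also assumptions.

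**The case against.** The strongest reply is that no sentence exempts controls. The exclusions appear once under Participants, consent is required of everyone, and the enrolment sentence is general. The contrary evidence is mainly the placement of one bracketed phrase in a summary table. That phrase also covers the inclusion criteria, so a literal reading would leave controls with no age limit and no consent requirement, which is unlikely to be intended. The flow diagram (Figure 2) is not available here and may settle the matter. An article may also leave coded definitions to a fuller protocol. The Table 5 task is not limited to one arm, so it does not show unequal application.

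Most of this stands. A reader might infer that sicker patients are known to remain in the control arm and that the comparison is therefore tilted toward the intervention. The documents do not support that: it is a plausible consequence of Table 4, not a stated fact, and late selection with consent could act the other way.

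The size is open to challenge too. The abstract and the specific objectives speak of admissions related to vascular disease. Patients excluded for immobility or non-vascular illness need not have two or three times the *vascular* admission rate. At the mild end the distortion is about 2%.

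The reply does not remove the inconsistency. If the exclusions do apply to controls, the Blinding section still has those controls selected after the intervention, under terms without a definition. Which patients are eligible in which arm, and when this is judged, is core protocol content rather than detail for an analysis plan.

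**Conclusion.** The point holds as an unresolved inconsistency with a real risk of bias in the primary outcome. It does not establish that controls were exempt, that the bias runs in one direction, or that it has a particular size.

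The article supports this much: the health exclusions are undefined, Table 4 attaches them and physician enrolment to the intervention group only, and controls are selected after the intervention. If the exclusions are not applied to controls, the comparison is biased toward the intervention. The spurious rate ratio of 0.98 to 0.71 is an illustration that rests on assumed f of 5-20%, assumed k of 1.5-3, and the disputed premise that no control is screened. If controls must survive and consent after the period, a bias against the intervention is possible (1.05 at an assumed 5% lost and twice the rate). The two mechanisms could not be separated afterwards from the outcome data alone.

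**What to change.** - Reconcile Participants; Randomization, allocation and implementation; Blinding; Table 4; and Informed consent, so that they state one eligibility and consent process for each arm.
- Express immobilization, serious ill health and short life expectancy as far as possible by fields and codes available in the electronic record. Which fields exist has to be confirmed, since the article does not list them.
- Run that same query on both sampling frames, as of a common index date, before any patient is drawn.
- In Table 4, place the inclusion and exclusion criteria over both groups.
- Report by arm the numbers sampled, excluded (with reason) and not enrolled, so that any remaining difference in consent or physician selection is visible.
- Use admissions of patients who were sampled but not enrolled only if ethics approval allows it without consent. Otherwise leave this out, because it conflicts with the consent requirement.

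The cost is protocol wording and a shared query, and study data already come from the electronic record. The downside is that coded criteria are coarser than clinical judgement, so some unsuitable patients may be drawn and approached. The change does not cure unequal consent between arms or the use of different sets of centers; those need their own handling.

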### Interventions

Organized intervention strategy aimed at patients and professionals:

1. Organized intervention strategy:

a) Informed active patient. By means of therapeutic education of the patient according to the CCM recommendations and following the Stanford EPP model. To promote patient autonomy: self-measurement of blood pressure and blood glucose control. Use of recommendations for patients in a uniform format and content for all the professionals using the recommendation forms for patients with chronic diseases (hypertension, diabetes, IHD, obesity, smoking) available in the electronic medical history.

a) Shared decision making. Personalized control objectives. To seek ways of promoting the increased participation of chronic patients in their treatment and the sharing of decisions. Creation of a patient follow-up record showing the state of the different study variables. The achievement of the objectives is evaluated with a traffic light type graph identifying the degree of compliance in the colors green, amber or red. Personalized and agreed objectives are established for each patient and shown on the record (see Figure 1). The IHD patient care protocol of the SVMFiC (2010 update) is used [19], available via the Abucasis intranet. The criteria used to define good control of the variables (Table 1) are those of the Cardiovascular Disease Prevention Group of the Preventive Activity and Health Promotion Program (PAPPS) [5].

a) Appointment planning. Every three months, although variable depending on the patient, to provide time to evaluate the agreed changes. At nurse/patient visits to assess: diet, exercise and therapeutic compliance at 2 weekly sessions every 3 months (Tables 2 and 3).

a) Primary care doctor-nurse teamwork. Joint work with agreed aims in a basic primary care health unit.

a) Actions based on scientific evidence. Work following electronically available protocols validated by scientific societies integrated in the Valencian Medical Institute. Communication with the cardiology service, to facilitate the interconsultation between primary and secondary care.

a) To promote information systems through a single electronic history shared between primary and secondary care. Evaluation of indicators of program follow-up.

a) Formative intervention strategy for professionals:

a) Formative. Four face-to-face workshops (every 3 months); monthly clinical session on cardiovascular disease; online tutorials with the cardiology service to solve any doubts. Face-to-face tutorials with a team, reference doctor/nurse, in each health center.

a) Strategies to avoid clinical inertia: carry out therapeutic changes if there is poor control before 3 months.

**Figure 1 F1:**
[figure not shown]
Personalized follow-up record.

**Table 1 T1:** Therapeutic objectives

** *Variable* **	** *Objective* **
** *Basal blood glucose* **	< 126 mg/dl
** *HbA1c* **	< 7%;
** *Blood pressure* **	≤140/90 mmHg
** *LDL cholesterol* **	≤ 100 mg/dl
** *Therapeutic compliance** **	80-110%
** *Practice of exercise* **	30 minutes per day > 3 days per week
** *Mediterranean diet* **	Validated survey.

(*)Pill count.

**Table 2 T2:** Primary care visit timeline

** *Visit timeline* **												
** *Follow-up months* **	**1**	2	3	**4**	5	6	**7**	8	9	**10**	11	12
** *Nurse* **	**√**		√	**√**		√	**√**		√	**√**		√
** *Physician* **	**√**			**√**			**√**			**√**		

**Table 3 T3:** Task distribution in the follow-up clinics

	** *Risk factors* **	** *Physician* **	** *Nurse* **
** *1* **	**Assess Abucasis register.**	++	++
** *2* **	**Establish personalized objectives.**	++	++
** *3* **	**Assess degree of control.**	++	++
** *4* **	**Assess therapeutic compliance.**	+	++
** *5* **	**Assess attitude towards each objective.**	++	++
** *6* **	**Agree interventions with the patient.**	++	++
** *7* **	**Adequate pharmacological treatment.**	++	-
** *8* **	**Individual intervention.**	++	++
** *9* **	**Team intervention.**	-	++
** *10* **	**Community intervention.**	-	++

### Outcome measures

Primary outcome measure: number of hospitalizations/cause. It is measured at the beginning and end of the study.

Secondary outcomes:

a) Level of control of CVRF: Blood pressure, LDL cholesterol, body mass index, basal blood glucose, HbA1c, therapeutic compliance (pill count), smoking. They are measured at each visit.

b) Healthy life habits: Exercise, mediterranean diet. They are measured at each visit.

c) Management: Number of annual primary care visits. It is measured at the end of the study.

To enhance the quality of measurements a training program is performed and there was one assessor for every three health centers.

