### Hypothesis

A multifactorial primary care intervention based on chronic models [12] can improve the level of control and reduce the number of hospital admissions in patients with IHD.

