### Sample size

The calculation of the sample size is carried out to compare means, with an alpha risk of 0.05 (95% confidence level) and a beta risk of 0.20 (80% power). For an estimated difference in SBP of 5 mmHg and a standard deviation of SBP of 2.5 mmHg, the number of persons necessary is 251 patients per group. Increased by 20% for possible losses, giving a total of 301 patients in each group.

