## Discussion

IHD is one of the main causes of death despite the great capacity for prevention that is available. Nowadays, multiple therapeutic tools of proven efficacy exist to control the main CVRF, as well as guidelines and protocols endorsed by the main scientific societies [5]–[7,19].

However, the degree of control of the CVRF in patients with IHD is low [15]–[17], which results in a higher use of health services. The frequency of primary care visits of a person with diabetes in Spain is 28 per year, even though this does not necessarily imply greater control [21]. Two of the main reasons for this are lack of treatment compliance and therapeutic inertia in the office, control of which has not improved in recent years [22]–[25].

The CCM [12] consider acting on these factors through new approaches. These models involve patient training to achieve greater autonomy and information, and the identification of high-risk patients to give them a more individualized and protocolized care.

Accordingly, the present study involved an organizational intervention based on CCM together with an educational intervention, integrating cardiology service professionals and primary care professionals (general practitioners and nurses), in an attempt to improve the degree of control of CVRF and decrease the number of hospitalizations.

This intervention aims to increase the degree of self-control for these patients as well as their ability for self-care and decision making to improve their long-term survival. At the same time, the greater degree of information and education can facilitate the increase in compliance that should result in an improvement in the therapeutic objectives.

The health care team-work methodology will be modified with more resolute and specific patient-centered office visits, without increasing the work load in the primary care offices. This is aimed at reducing clinical inertia.

The Abucasis computer system, available in secondary and primary care offices, facilitates the interaction between levels of health care as well as being a common and unique site for the patient to record and control the main CVRF.

The validity of the results, which depends on the representativeness of the sample, is controlled by the selection criteria designed and in relation to study power, through the sample size calculated taking into account any unexpected loss by controlling the random error.

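### The only stated power (80%, 251 per group) is for mean systolic pressure, a secondary outcome; the declared primary outcome, hospitalizations, has no power basis

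*Protocol article*

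**What the plan says.** Under Outcome measures the article states: "Primary outcome measure: number of hospitalizations/cause". Blood pressure appears in the same section as part of the first secondary item: "a) Level of control of CVRF: Blood pressure, LDL cholesterol, body mass index, basal blood glucose, HbA1c".

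The Sample size section holds the only calculation. "The calculation of the sample size is carried out to compare means", with alpha 0.05 and 80% power. The effect is introduced by "For an estimated difference in SBP of 5 mmHg", with a standard deviation of 2.5 mmHg. The result is 251 per group, raised by 20% to 301. Table 4 (Follow-up) gives 350 per group.

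The Hypothesis says that the intervention "can improve the level of control and reduce the number of hospital admissions in patients with IHD". The Discussion says that validity is controlled "in relation to study power, through the sample size calculated taking into account any unexpected loss", without naming an outcome.

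**The concern.** The outcome that was sized is not the outcome declared primary. No admission rate, target reduction or detectable effect for hospitalizations appears anywhere in the article. This is not a detail that a condensed article leaves to a fuller document: the article has a sample-size section, and that section concerns a secondary outcome.

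What is at stake is the meaning of a non-significant primary result. A general power statement in the Discussion, with nothing to limit it to SBP, invites the reader to treat the trial as adequately powered for its main question. A confidence interval wide enough to include a useful reduction in admissions could then be reported as evidence of no effect.

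**Working it through.** **1. The plan's own figure.** Inputs from the Sample size section: difference 5 mmHg, SD 2.5 mmHg, alpha 0.05 (taken as two-sided), power 80%.

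n per group = 2 × (1.960 + 0.842)² × (SD/difference)²

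- As printed: 2 × 7.849 × (2.5/5)² = 3.9, so 4 per group, not 251.
- With SD 20: 2 × 7.849 × (20/5)² = 251.2, which agrees with the stated 251. That an SD near 20 was used is an inference.
- Losses: 251 × 1.2 = 301.2, which reproduces 301.

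Whichever SD was used, the calculation concerns SBP. Correcting it would still leave hospitalizations unsized.

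**2. Power for hospitalizations.** The article gives no rate or reduction, so both are assumed: control rates μ0 of 0.2, 0.3 and 0.5 admissions per patient-year, one year of follow-up (Study design), and rate ratios (RR) of 0.80 and 0.70. The group sizes are the document's: 251 (after all allowed losses), 301 (planned) and 350 (Table 4, no losses).

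Variance of log RR = [(1/μ0 + k) + (1/μ1 + k)]/n, where μ1 = RR × μ0 and k = 0 for Poisson counts.

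Power = Φ(|ln RR|/SE − 1.960)

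Example with μ0 = 0.3, RR = 0.80, n = 251: variance = (3.333 + 4.167)/251 = 0.02988 and SE = 0.1729. Then 0.2231/0.1729 − 1.960 = −0.669, and power = 25%.

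| n per group | Reduction | μ0 = 0.2 | μ0 = 0.3 | μ0 = 0.5 |
|---|---|---|---|---|
| 251 | 20% | 18% | 25% | 38% |
| 301 | 20% | 21% | 29% | 45% |
| 350 | 20% | 24% | 33% | 50% |
| 251 | 30% | 37% | 51% | 73% |
| 301 | 30% | 43% | 59% | 80% |
| 350 | 30% | 48% | 65% | 86% |

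**3. Rate ratio detectable with 80% power** (same formula, solved for RR, k = 0):

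| n per group | μ0 = 0.2 | μ0 = 0.3 | μ0 = 0.5 |
|---|---|---|---|
| 251 | 0.51 | 0.59 | 0.67 |
| 350 | 0.57 | 0.65 | 0.72 |

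**4. What lowers power.** With overdispersion (k = 1, assumed) and n = 251, power for a 20% reduction falls to 16%, 21% and 28%. Intervention patients come from 15 centers, about 301/15 = 20 each. For assumed intracluster correlations of 0.01 and 0.05, the design effect in that arm is 1 + 19.1 × 0.01 = 1.19 and 1 + 19.1 × 0.05 = 1.95. The sample-size section shows no allowance for this.

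**5. What raises power.** Frequent events or large effects change the picture. At n = 251 (Poisson), a 40% reduction has 60%, 77% and 94% power at the three rates. For a 20% reduction to reach 80% power, the control rate would have to be about 1.4 per patient-year at 251 per group, or 1.0 at 350.

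**The case against.** The strongest reply is that nothing in the Sample size section presents the 80% as power for hospitalizations. It names SBP openly, and the Discussion sentence names no outcome. Risk-factor control is also half of the hypothesis, so sizing on SBP is not unrelated to the trial's aims. Admissions come from electronic records, so they may be lost less often than measured pressures, and 301 or 350 may be closer to the analysed number than 251.

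Much of this stands. A reader might infer that the trial has far less power for its primary outcome, or that a null hospitalization result is likely even if the intervention works. The document supports neither as fact. Both need an admission rate and a worthwhile reduction, and it gives neither. Power at 350 per group with 0.5 admissions per year and a 30% reduction is 86%. To quote only a 20% reduction at the smallest group size would pick the low end.

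The reply does not remove the mismatch. The primary outcome still has no power basis, and the Discussion still appeals to the calculated sample size without limiting the claim to SBP.

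**Conclusion.** The point holds as a mismatch that can be read from the text: the stated 80% and the 251 and 301 per group belong to a secondary outcome, and the declared primary outcome has no power basis. This part needs no assumption.

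Its size is conditional. Under the assumed Poisson rates, power for a 20% reduction stays at or below about 50% across all the document's group sizes. For a 30% reduction it passes 80% only at the highest assumed rate with 301 or more per group. Low power is therefore a serious possibility, not an established fact.

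**What to change.** - **Sample size section:** state that the 80% power does not apply to the primary outcome. Add the hospitalization rate ratio detectable at 80% power for the fixed group size, under a stated control rate, and say how overdispersion and clustering are treated. The group size must be settled first, since this section gives 301 and Table 4 gives 350.
- **Before restating 251 for SBP:** reconcile it with its printed inputs. SD 2.5 gives about 4 per group; SD 20 would give about 251.
- **Discussion:** limit the power statement to SBP.
- **Reporting:** commit to a rate ratio with 95% CI for hospitalizations, and to not reading non-significance as no effect.

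Making SBP primary should not be treated as a routine wording fix. In a registered, ethics-approved open trial whose controls are selected after the intervention, it would change the main question and raise concern about outcome switching.

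The cost is wording and a short calculation, with no extra patients. The downside is that the stated power for the primary outcome becomes less favourable.

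### Secondary outcomes are measured at visits described only for the intervention arm, so the stated measurement rule cannot be applied to controls chosen afterwards from records

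*Protocol article*

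**What the plan says.** All references are to the protocol article.

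- **Outcome measures, risk factors.** The list is blood pressure, LDL cholesterol, BMI, basal glucose, HbA1c, compliance and smoking. It ends "therapeutic compliance (pill count), smoking. They are measured at each visit".
- **Outcome measures, habits.** "Healthy life habits: Exercise, mediterranean diet. They are measured at each visit". Neither rule names an arm.
- **Outcome measures, visit count.** "Management: Number of annual primary care visits. It is measured at the end of the study".
- **Interventions.** The visit schedule is a component of the intervention: "Appointment planning. Every three months, although variable depending on the patient, to provide time to evaluate the agreed changes". Nurses assess three of the outcomes there: "At nurse/patient visits to assess: diet, exercise and therapeutic compliance at 2 weekly sessions every 3 months".
- **Table 2.** Nurse and physician contacts are ticked by follow-up month.
- **Table 4.** First, second and third visits appear under the intervention follow-up row. The control entry gives only the sampling of patients from the records of 72 centres.
- **Blinding.** "the control group is selected after the intervention is made but for the same period of time".
- **Participants.** The electronic health record is named as the data source, without restriction to one arm.
- **Discussion.** The new way of working is meant to operate "without increasing the work load in the primary care offices".

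**The concern.** A rule that measures outcomes at each visit needs visits in both arms. Here they are part of what is being tested, and patients picked after the year has passed cannot have attended them.

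Two consequences follow. For assessments made specifically at the intervention's nurse visits, a between-group comparison may have nothing on the control side. For variables that routine care may also record, intervention values arise on a schedule, while no schedule is described for controls. If controls are measured less often, or mainly when something prompts it, the groups can differ in recorded risk-factor control for reasons unrelated to the intervention.

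The visit count raises a related problem of interpretation. The intervention adds scheduled contacts and then counts contacts as an outcome.

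**Working it through.** **Step 1. Which outcomes depend on visits.** Seven risk-factor items plus two habits give 7 + 2 = 9 outcomes measured at each visit.

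**Step 2. Whether controls have such visits.** Appointment planning is listed under Interventions, Table 2 gives its timeline, and Table 4 places its visits in the intervention follow-up row. No visit is described for controls, and the Blinding section has them selected afterwards. That the visits belong to one arm is inferred from these places together; nothing in the article supports another reading.

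**Step 3. Which outcomes have a possible control source.** The electronic record can plausibly supply blood pressure, LDL, HbA1c, glucose, BMI and smoking in both arms: 6 of 9. For pill count (the compliance method in Table 1), exercise and the Mediterranean diet survey, 3 of 9, no control source or time point is stated. The Informed consent section requires every patient's consent, so a later contact with controls is not excluded. It could not recreate pill counts over the past year or baseline habits.

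**Step 4. Whether the rule is clear within the intervention arm.** Table 2 marks eight months with a visit and Table 4 names three visits. The two need reconciling before a measurement at each visit has one meaning.

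**Step 5. What missing control values would cost.** The article does not say how many controls have a usable value, so this is an illustration. Assumptions: blood pressure difference 5 mmHg, 251 intervention patients, a fraction *f* of 251 controls with a value, two-sided alpha 0.05, SD 20 mmHg. SD 20 is used because it gives 252 per group, close to the stated 251; the printed SD of 2.5 gives 4 per group, which is a separate matter.

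Power = Φ( 5 / [20 × √(1/251 + 1/(251*f*))] − 1.96 )

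| *f* | Controls with a value | Power |
|---|---|---|
| 1.00 | 251 | 80% |
| 0.75 | 188 | 74% |
| 0.50 | 126 | 63% |
| 0.25 | 63 | 43% |

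This is loss of precision only. Bias from selective recording would come on top and cannot be sized from the article.

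**Step 6. How much of the visit count is scheduled.** Table 2 ticks the nurse in months 1, 3, 4, 6, 7, 9, 10 and 12 (8) and the physician in months 1, 4, 7 and 10 (4). That is 8 + 4 = 12 contacts in 8 distinct months. The article's only usual-care frequency is 28 visits a year, for people with diabetes (Discussion):

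- 12/28 = 43%, counting contacts
- 8/28 = 29%, counting visit-months

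The schedule would exceed half of all visits only if the annual total were below 24 (contacts) or 16 (visit-months).

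**Step 7. Whether the schedule alone could produce a difference.** Assume an SD of 8 visits and 251 per group, and let a share of scheduled contacts replace ordinary ones. Net excess = (8 to 12) × (1 − share replaced).

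| Share replaced | Net excess visits | Power to detect it |
|---|---|---|
| 50% | 4 to 6 | about 100% |
| 75% | 2 to 3 | 80% to 99% |
| 90% | 0.8 to 1.2 | 20% to 39% |

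Unless most scheduled contacts replace ordinary ones, a significant difference in total visits could arise from the schedule alone.

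**The case against.** The best defence is that the article names the electronic record as its data source for everyone, and that controls cover the same calendar period. Blood pressure, laboratory values, BMI, smoking and visit counts then have a source in both arms, and unequal recording is a risk to manage. This stands. A reader might infer that all the secondary comparisons are invalid; the article does not support that.

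A second defence is that analysis windows and completeness tables belong in a statistical analysis plan or fuller protocol. That would answer a complaint about missing detail. It does not answer this point: the article states a measurement rule, and its own account of control selection makes that rule inapplicable to one arm.

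Third, a reader might conclude that no control data exist for pill count, exercise and diet. The article does not say what the records hold. Only the absence of a stated source is established. A retrospective pill count is implausible; exercise and diet are less certain.

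Fourth, a reader might say that the visit outcome is largely set by the schedule. That is not shown. The contacts are 29% to 43% of the only frequency given, which comes from a different patient group, and the schedule may vary by patient. Total visits are also a legitimate measure of workload, which the Discussion says should not rise, so programme visits belong in the total.

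**Conclusion.** The concern holds in a limited form. The rule of measuring at each visit cannot be carried out for controls. Three of nine visit-measured secondary outcomes lack a stated control source. The other six can be compared if the record holds them in both arms, with a risk of differential ascertainment whose size the article does not allow one to estimate. In the illustration, power falls from 80% to 63% if half the controls have a usable value, assuming SD 20 mmHg and a 5 mmHg difference.

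Total annual visits remain a sound resource-use outcome. Up to 12 contacts are scheduled in the intervention arm, so a difference does not show a change in other demand.

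The conclusion rests on reading the described visits as the intervention's own. It concerns secondary outcomes only.

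**What to change.** 1. Restrict between-group comparisons of these secondary outcomes to variables taken from the electronic record in both arms.
2. Use one common window for both arms, for example the value nearest month 12 within ±3 months, and report by arm the share of patients with a value.
3. Report pill count as within-group description only. Do the same for exercise and diet unless the records are shown to hold them for controls.
4. Keep total annual visits as a resource-use outcome. State that it includes up to 12 contacts scheduled by the intervention (Table 2), and that a difference is not evidence about other demand.
5. Optionally, show scheduled visits separately as description. A formal test of the remaining visits is not advised: every control visit would count as unscheduled, while scheduled contacts may replace ordinary ones in the intervention arm, which would favour the intervention.
6. Reconcile the visit numbers in Table 2 and Table 4.

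The cost is a change of wording in the outcome and analysis sections and fewer formal comparisons. No new data collection is needed.
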